# Feasibility and usability of remote transcranial direct current stimulation (tDCS) for self-regulation in children with autism: protocol for a randomized controlled pilot study

**DOI:** 10.1186/s40814-025-01650-4

**Published:** 2025-04-29

**Keywords:** Neurostimulation, Autism spectrum disorder, Children, Self-regulation, Transcranial direct current stimulation, Feasibility, Pilot study, Usability

## Abstract

**Background:**

Autism spectrum disorder (ASD) is a neurodevelopmental disorder characterized by social communication and self-regulation impairments. Impaired response inhibition and self-regulation in ASD have been shown to be related to abnormal functional network connectivity in the dorsolateral prefrontal cortices (DLPFC). Transcranial direct current stimulation (tDCS) of DLPFC is a safe, tolerable, and precise intervention that has shown promise for the improvement of self-regulatory behavior in ASD. However, clinical translation has been prevented by a lack of effective systematic design, experimental control, and a high participation burden. The proposed protocol aims to evaluate the feasibility and usability of home-based tDCS to promote self-regulation in children with ASD.

**Methods:**

Participants will be randomized into an active or sham tDCS group and will receive 20 min of stimulation 5 days per week for 3 weeks. Participants in the sham group receive a negligible amount of stimulation. Sessions will be virtually supported by the study team. Assessments are taken at baseline, 1-week post-treatment, and 18 weeks post-treatment. These assessments include clinical measures of self-regulation and social communication (participant-, parent-, and clinician-reported), a response inhibition task, and magnetic resonance imaging. Recruitment, retention, and adherence rates will be used to assess the feasibility of the protocol. The usability of the remote tDCS device will be assessed via a usability survey, user interviews, and video analysis of device use.

**Discussion:**

Home-based tDCS may benefit children by providing an efficient, passive, and tolerable treatment that positively impacts function, activities, and participation. This study will identify potential challenges for the clinical translation of this therapy so that home-based tDCS can be positioned for success in healthcare delivery implementation.

**Trial registration:**

ClinicalTrials.gov, NCT06129058. Registered on November 8, 2024.

**Supplementary Information:**

The online version contains supplementary material available at 10.1186/s40814-025-01650-4.

## Background

Autism spectrum disorder (ASD) is a neurodevelopmental disorder that affects 1% of children globally [1], resulting in emotional and economic burdens on families and creating a high demand for intensive resource support in health care systems [2]. ASD encompasses a wide range of symptoms, including cognitive, social communication, and self-regulation challenges. The combination and severity of these symptoms varies across individuals, resulting in significant heterogeneity [3]. Self-regulation is a key mechanism underlying many of the behavioral challenges experienced by individuals with ASD and is defined as the ability to control, monitor, and manage emotions, cognition, and behaviors in a goal-oriented manner [4]. Key components of self-regulation include response inhibition, which is the ability to suppress contextually inappropriate responses, and emotional regulation, which is the ability to modify arousal and reactivity to engage in adaptive behavior [5]. Self-regulation is strongly correlated with the development of social communication skills, mental health outcomes, and academic achievement in children with ASD [6, 7]. Impaired self-regulation is a predictor of quality of life and companionship in adulthood and is associated with increased parental stress, family and peer discord, and risk of social stigmatization [8, 9]. There is a lack of effective interventions for the promotion of self-regulation in children with ASD and behavioral interventions are often time and resource-intensive for families and providers and yield small effect sizes for patient-reported outcomes [10]. Children with ASD, their families, caregivers, and clinicians have identified the urgent need to establish novel, effective interventions that promote self-regulation [10].

Impairments in response inhibition play a prominent role in self-regulation in ASD and the co-morbid disruptive, compulsive, aggressive, and self-injurious behaviors that are associated [11–13]. The neural mechanisms for self-regulation are relatively well established and are defined by fronto-subcortical and fronto-limbic networks [14, 15]. These neural networks are compromised in ASD as characterized by an overgrowth of brain volume in early neurodevelopment, which may lead to local hyperconnectivity in frontal and occipital regions, and long-range hypoconnectivity between frontal regions and other cortical areas [16]. Specifically, the dorsolateral prefrontal cortices (DLPFC) and inferior frontal gyri are commonly reported to have abnormal functional network activity patterns relative to controls that are indicative of poor top-down response inhibition and self-regulation in this population [12, 17].

Transcranial direct current stimulation (tDCS) is a safe, tolerable, and precise intervention that can target these neural networks and has shown promise for the reduction of ASD symptoms. It runs a current through target brain regions via an anode and a cathode. The magnitude of the electric field elicited by tDCS has been shown to be sufficient in modulating neural activity on a cortical network level [18]. This is due to the coupling mechanisms of local endogenous fields, which result in the amplification of the electric field produced by tDCS [19]. Open-label and waitlist-controlled studies have indicated that neuromodulation of prefrontal regions results in improvements in response inhibition on neural signatures (e.g., MER ratio), cognitive tasks (e.g., Go/NoGo), social communication measures, Autism Treatment Evaluation Checklist (ATEC) sociability sub-scores, and parent-reported clinical health outcomes (e.g., reduced compulsive, aggressive, and self-injurious behaviors) [20, 21].

Clinical translation of tDCS has been prevented by a lack of systematic design and experimental control, small and poorly represented samples, inadequate blinding, insufficient follow-up periods, and a paucity of patient-reported outcome measures [22, 23]. Further, the participation burden was extremely high in previous studies examining tDCS, as they required multiple trips to the laboratory. Home-based tDCS has the potential to benefit children with ASD by providing an efficient, passive, accessible, and tolerable treatment that positively impacts function, activities, and participation. However, there is limited research investigating tDCS in this population and no studies examining home-based tDCS specifically. To address this gap, a neurobiologically informed pilot study is needed to determine if it is feasible, tolerable, and acceptable to pursue a full-scale randomized control trial (RCT) to test if home-based tDCS therapy is efficacious for improving self-regulation across multiple levels of integration (cognitive, behavioral, neural) in children with ASD.

## Methods

### Design

This study is a double-blind pilot RCT examining the feasibility of carrying out a full-scale RCT to determine if 15 sessions of home-based tDCS therapy can improve clinical, cognitive, and neural outcomes associated with self-regulation in children with ASD. Measures are taken at baseline (T0), 1-week post-treatment (T1), and 12 weeks post-treatment (T2).

### Participants

#### Recruitment

Children with ASD with self-regulation impairments (*n* = 46) aged 9–18 years will be recruited from the Province of Ontario Neurodevelopmental Disorders Network (POND) (www.pond-network.ca). The lower limit of nine years old was determined based on previous studies investigating the safety and tolerability of non-invasive brain stimulation (NIBS) in children with ASD [24, 25]. POND participants have an existing research-reliable ASD diagnosis based on DSM-V criteria, informed by the gold standard Autism Diagnostic Observation Schedule (ADOS) [22] and the Autism Diagnostic Interview – Revised (ADI-R) [26]. Recruitment flyers will be sent to POND families with study information and contacts. Potential participants will be contacted by a research assistant until the recruitment target is reached.

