### Sample size

Pilot RCTs do not test efficacy, and formal sample size calculations are not typically used. However, if too small, a pilot study may underestimate the standard deviation leading to underpowered efficacy RCTs. Sim et al. [30] suggested that the sample size of a pilot study be determined based on the desired level of confidence for the standard deviation of the primary outcome measure in the larger-scale RCT, and the power and significance level anticipated. Additionally, attempts to minimize the total sample size required should be made. Given an expected 10% loss to follow-up, and to maintain equal group sizes, the proposed pilot sample size will be *n* = 46. This is adequate to assess recruitment success and feasibility issues and provides sufficient data for exploratory analysis of the secondary outcomes.

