### Randomization and blinding

Participants will be randomized to either the active tDCS or sham tDCS treatment condition in a 1:1 allocation ratio. An independent research assistant will prepare a randomization schedule using random permuted blocks of varying sizes to ensure allocation concealment and will assign participants to active or sham tDCS groups. Block sizes and variations will only be known to the independent research assistant. The allocation sequence will be entered into a password-protected Excel sheet. A separate, blinded member of the study team will enroll participants. Participants, family members, assessors, and investigators will all be blinded to group allocation. The devices will be preprogrammed with codes that correspond to specific stimulation parameters. During each session, participants will be provided with a code aligning with their group assignment to maintain blinding. Unblinding of participants will be permissible if the participant is no longer participating in study procedures and requires information on group allocation for medical purposes. In this case, the principal study investigator will reveal group membership to the participant. To minimize observer bias, the principal investigator will not be involved in data collection or analysis.

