### Primary outcome measures

The primary objectives of this study are to assess the feasibility, tolerability, and acceptability of an RCT to test the efficacy of tDCS. Feasibility measures are based on a hypothetical sample size of 100 participants for a full-scale RCT, based on previous neurostimulation clinical trials [47–51].

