#### Feasibility

Feasibility measures include recruitment rate, retention rate, adherence rate, and success of randomization and blinding. Recruitment and attrition will be calculated using the electronic audit trail generated by the documentation kept by the independent RA and statistician and research assistant. Adherence will be calculated based on the number of sessions attended and completed by participants who complete all assessments. The success of blinding will be determined based on responses to the questions “What group do you think you were in?” and “How sure are you?”, which will be asked on the follow-up tolerability questionnaire (adapted from Garvey et al., 2001) [52]. Descriptive statistics will be completed to establish if the comparison and intervention groups are similar in age, gender, ASD severity, and clinical symptom severity. The success of randomization will be determined by evaluating group differences in sex distribution and median age. Randomization will be determined to be successful if the differences in sex distribution are within ± 2 participants, and the median age difference is within ± 2 years.

The feasibility of the optional MRI component will be evaluated based on total and successful attempts at completing the MRI protocol. There is a paucity of data on neural outcomes in this population; therefore, any amount of data collected is valuable. Previous MRI studies examining children with ASD include samples between 20 and 50 participants [53–57]. In a hypothetical sample size, *n* = 100 (*n* = 50 per group) for a full-scale RCT, including data from at least 20 individuals in each group would be sufficient to conduct an analysis. Given this, the optional MRI component of this study will be feasible if ≥ 20% of participants in each group have successful MRIs. A successful attempt is one in which a majority of the scan is completed with minimal motion artifact as determined by the MRI technician.

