### Data analysis

#### Primary measures analysis

##### Feasibility

Feasibility measures will be analyzed as per the progression criteria outlined in Table 1. These criteria were determined based on recommendations by Avery et al. to assess whether to proceed with a full-scale RCT [75]. Associations between participant characteristics (e.g., age, IQ, travel distance) and ability to complete all trial tasks will be examined to inform the planning of a large-scale RCT. *T*-tests will be conducted for associations with continuous variables (e.g., IQ, age, travel distance). Chi-squared tests will be conducted for associations with categorical variables (e.g., gender).

**Table 1 Tab1:** Progression criteria for feasibility metrics

	**GO–proceed with RCT**	**AMEND–proceed with changes**	**STOP–do not proceed unless changes are possible**
Recruitment target	*n* = 46	*n* = 36–45	*n* < 36
Adherence	≥ 90% of tDCS sessions are completed by participants who complete all assessments	70–89% of tDCS sessions are completed by participants who complete all assessments	< 70% of tDCS sessions are completed by participants who complete all assessments
Participant retention	≥ 90% retention	80–89% retention	< 80% retention
Optional MRI target	≥ 20% of participants have successful MRIs in each group	10–19% of participants have successful MRIs in each group	< 10% of participants have successful MRIs in each group

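### The recruitment progression row in Table 1 scores a bare count with no stated point of judgement, although the article names a recruitment rate and refers feasibility to a trial of 100

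*Protocol article*

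**What the plan says.** All references are to the protocol article.

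- **Measure named.** Under Primary outcome measures, Feasibility: "Feasibility measures include recruitment rate, retention rate, adherence rate, and success of randomization and blinding". The Abstract (Methods) also lists recruitment among the rates used to assess feasibility. On calculation, the Feasibility section says: "Recruitment and attrition will be calculated using the electronic audit trail". No unit of time and no denominator is attached.
- **Reference size.** The opening of Primary outcome measures says: "Feasibility measures are based on a hypothetical sample size of 100 participants for a full-scale RCT".
- **Decision rule.** Under Data analysis, Feasibility, the measures are to be analysed by the criteria in Table 1. The row labelled "Recruitment target" reads n = 46 for GO, n = 36–45 for AMEND and n < 36 for STOP. The adherence, retention and MRI rows are all percentages.
- **When recruitment ends.** Under Participants, Recruitment: "Potential participants will be contacted by a research assistant until the recruitment target is reached". The source named is one provincial network.
- **Origin of 46.** The Sample size section says: "Given an expected 10% loss to follow-up, and to maintain equal group sizes", "the proposed pilot sample size will be" 46.

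**The concern.** A pilot's recruitment criterion should tell the sponsor whether the full trial can be filled in a workable time. That needs a count over a period, a yield from those approached, or both. Here the text names a rate and the decision uses a count. The same count also tells the team to stop contacting families. Followed as written, a fast pilot and a slow one both end at 46 and both read GO.

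AMEND and STOP can arise only if recruitment ends short of 46, and the article names no date or event at which that would be established. Recruitment is the first row of the progression table, so the decision on the full trial could rest on a GO that carries little information about reaching 100.

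**Working it through.** **1. The plan's own figure.** The Sample size section gives no base number, only the 10% loss and equal arms ("randomized to either the active tDCS or sham tDCS treatment condition in a 1:1 allocation ratio"), so 46 can be checked for consistency but not reproduced.
- Base 40: 40/0.9 = 44.4, rounded up to 45, then 46 for equal arms.
- Base 41: 41/0.9 = 45.6, rounded up to 46.

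The figure is plausible and is not disputed.

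**2. What the cut-offs refer to.** 36/46 = 78.3% and 45/46 = 97.8%. The AMEND band runs from 78% to 98% of the pilot's own target. Neither bound is a rate, and neither is derived from 100. The Feasibility section applies the reference size of 100 explicitly only to the MRI criterion.

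**3. Accrual speeds that score GO.** If the pilot takes T months to reach 46 and the full trial recruits at the same pace, months to 100 = (100/46) × T = 2.17 × T. The article gives no T, so the values below are assumptions.

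| Assumed T (months) | Rate per month | Table 1 result | Months to 100 |
|---|---|---|---|
| 12 | 46/12 = 3.83 | GO | 26.1 |
| 24 | 46/24 = 1.92 | GO | 52.2 |
| 36 | 46/36 = 1.28 | GO | 78.3 |

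A count of 46 has an exact Poisson 95% CI of 33.7 to 61.4. With T = 24, the projection is therefore 52 months (100 × 24/61.4 = 39 to 100 × 24/33.7 = 71). Even this needs the duration that the row omits.

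**4. Yields that score GO.** If A families are approached to obtain 46, approaches needed for 100 = 100 × A/46. With assumed A = 60, 150 or 460, this gives about 131, 327 or 1000. All three read GO.

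**5. Would a window help?** Take an assumed 24-month window and Poisson accrual, and keep the existing cut-offs.

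| True rate per month | Expected count | GO (46 or more) | AMEND (36–45) | STOP (<36) |
|---|---|---|---|---|
| 1 | 24 | <0.1% | 1.3% | 98.7% |
| 1.5 | 36 | 6.1% | 46.1% | 47.8% |
| 2 | 48 | 63.3% | 33.6% | 3.1% |
| 3 | 72 | >99.9% | <0.1% | <0.1% |

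Once there is a closing date, the row separates slow from fast accrual. Whether 46 and 36 are then the right cut-offs depends on the time to 100 that is acceptable, which the article does not state.

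**The case against.** The strongest reply is that this is a condensed article and the full protocol may give an accrual period. It may, and its absence here is not the point. Table 1 sets out all three bands and is named as the rule by which feasibility will be analysed. A period held elsewhere does not enter that rule unless the row refers to it.

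A second reply is that the Recruitment sentence is simply a cap: stop contacting at 46. The existence of AMEND and STOP bands presupposes that recruitment can fall short. The pool is one network, narrowed by age, severity score, stable medication and contraindications, so it can run out, as can funding or study time. This stands. A reader might infer that GO is guaranteed by the design, and the documents do not support that: nothing promises unlimited time, and a shortfall would carry information.

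A third reply is that recruitment is logged in an audit trail and that factors influencing participation and refusal are a secondary objective. This also stands in part. A reader might infer that the pilot will learn nothing about recruiting 100, and that goes too far, because a rate can be worked out afterwards. But no threshold applies to that rate, so it cannot change the Table 1 result.

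Finally, the durations and numbers approached above are assumptions, and the projection supposes that the full trial recruits at the pilot's pace. The article does not say where the full trial would recruit. The figures show how much the row leaves undetermined; they do not predict this trial's accrual.

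**Conclusion.** The mismatch is real. A rate is named and 100 is the reference, but the decision uses a bare count, contact continues until that count is reached, and the article gives no point for judging a shortfall. GO is compatible with very different accrual speeds: each extra year of pilot accrual adds about 26 months to the projected time to 100 without changing the result. The row therefore informs poorly, though not emptily, on whether the full trial can be recruited.

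The factor of 2.17 follows from the documents' own 46 and 100 and assumes an unchanged pace; the months rest on assumed durations. Participant safety and the other Table 1 rows are unaffected. The row should be corrected before the progression decision is taken.

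**What to change.** Restate the recruitment row as a rate:

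1. Tie the counts to the pilot's planned accrual period of T months and judge the row when that period closes. If 46 is reached earlier, use 46 divided by the months taken.
2. State the time M, in months, within which recruiting 100 would be acceptable. The rate needed is 100/M per month, or a count of 100 × T/M in the pilot period. Set the GO cut-off from this, and the AMEND/STOP boundary from the longest M that would still be workable with changes. Adding a window alone is not enough. Keeping 46 and 36 would imply accepting 100/46 = 2.17 and 100/36 = 2.78 times T, and the sponsor should either say so or change the cut-offs.
3. Beside the row, report the number randomised out of those eligible and approached, with a 95% CI.

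The cost is one table row and a sentence or two in the Recruitment and Feasibility sections. Sample size, randomisation and treatment do not change. The team should confirm that the audit trail records approaches and eligibility, because the article says only that recruitment will be calculated from it. The downside for the sponsor is that GO becomes possible to miss.

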#### Eligibility

Self-regulation impairment will be defined by a score of four or greater on items 4 (disruptive behavior) or 5 (restricted and repetitive behavior) on the Clinical Global Impressions Severity (CGI-S) administered by a physician during screening [27]. As this is a feasibility study, there will be no intelligence quotient (IQ) cut-off for participation. It is critical that novel treatments for response inhibition and self-regulation be studied in the broader autism community, as children with lower IQs more frequently exhibit social impairments and self-regulation challenges [28, 29], and are not typically candidates for behavioral treatments that require high learning demands and cognitive effort. Children with safety contraindications for tDCS (e.g., seizure disorder), magnetic resonance imaging (MRI) (e.g., metal in situ), or co-morbid neurological disorders (e.g., epilepsy, stroke, brain tumor) will be excluded. Children must not have had any changes to their medications for at least 6 weeks prior to the baseline assessment (T0) and no planned medication changes during the study. Children with prior tDCS experience will be excluded to ensure blinding.

### Consent

Consent will be obtained electronically using the REB-approved documents via REDCap or in person. In-person consent will be conducted by a designated study team member who will complete the capacity assessment and consent discussion. If the participant does not successfully complete the capacity assessment their parent/substitute decision maker will be given the option to sign the parent consent, and the participant will be provided the option to sign the assent form. Electronic consent will follow the same format; however, the designated study team member will complete the capacity assessment and consent discussion, as well as answer any questions, at a scheduled BRI videoconferencing (Zoom) session with the participant and their parent/guardians. Prior to attending the scheduled consent discussion, participants and their families will be provided a read-only copy of the consent document to review together. Non-verbal consent or assent will be documented appropriately as needed.

